### Data management

To measure the health effect of the whole intervention package at the population level, there will be two cross-sectional surveys (before and after, 12 months apart). Data will be collected on demographic and socioeconomic variables, behavioral risk factors such as tobacco and alcohol use, anthropometric measurements such as height and weight, and clinical measurements such as blood pressure and random blood glucose. Four cadres of field staff will be involved in data collection. These include field interviewers, CHWs, field assistants and supervisors.

Field interviewers will be trained by the SCALE UP study investigators to collect the demographic, socioeconomic and behavioral risk factor data using structured interviews during the cross-sectional surveys in both the intervention and control sites. In the intervention site, the anthropometric and clinical measurement will be performed by CHWs. In the control site, however, measurements will be performed by trained field assistants rather than CHWs. This is because CHWs are considered to be part of the intervention. Each interview is estimated to last approximately 30 min, followed by the physical and clinical measurements. The field staff will be instructed to follow standard procedures for all measurements as outlined in the WHO STEPS manual [37]. Specifically, while taking the blood pressure, field staff will be required to ensure that the respondent remains seated for about 5 min, with no talking, holding the monitoring device on the upper arm and holding it at heart level against his/her chest. The blood pressure will be measured three times, using the left arm. To minimize observer bias, validated digital equipment will be used, the OMRON M6® (Digital Automatic Blood Pressure Monitor). Note that referral of participants for further management will be based on the average of the three blood pressure measurements (systolic ≥140 and/or diastolic ≥90 mmHg).

At the intervention clinic, additional information will be collected on clinic attendees to monitor their progress and evaluate the effect of the intervention on blood pressure control and overall CVD risk profile. Baseline interviews will be conducted with each clinic attendee by trained field interviewers. Immediately after an interview, nurses at the clinic will record physical and clinical measurements for each clinic attendee. These measurements will be repeated each time the participant attends the intervention clinic over a period of at least 12 months. At the end of this period, an endline interview will be conducted with each clinic attendee. Table 2 summarizes the data to be collected over the intervention period.

**Table 2 T2:** Data collection schedule

**Data**	**Baseline**	**Ongoing**	**Endline**
** *Population based* **	X		X
Socio-demographic characteristics	X		
CVD behavioral risk factors	X		X
Physical measurements (weight, height, waist and hip circumference, blood pressure)	X		X
Blood testing (glucose)	X		X

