#### (1) Raising awareness and (2) improving access to screening

The first two components of the intervention package include door-to-door household visits by community health workers (CHWs) to raise awareness about CVD risk and to conduct screening of each eligible adult aged 35 years and above in the intervention slum in order to determine their individual CVD risk profile. CHWs are typically community-based volunteers who have an interest in community health. They are usually well known by the community and most have received some form of basic training in community health activities such as peer health education for HIV/AIDS prevention. The SCALE UP study will recruit CHWs to represent each of the eight villages in the intervention slum. These CHWs will then be trained and equipped to perform the door-to-door visits and screening exercise in their respective villages in the intervention slum.

Two weeks prior to the commencement of the screening exercise, there will be public awareness campaigns organized by the CHWs in each village of the intervention slum. This awareness campaigns will take place at community gatherings (known locally as *barazaas*). At these *barazaas*, CHWs together with village leaders will inform the audience about the burden of CVD in the community and the need to participate in the door-to-door screening. Additionally, CHWs will visit religious gatherings, usually held at local churches and mosques, to provide the same information. Such gatherings are usually well attended by respected members of the community who will then pass the information on to others. Finally, radio jingles announcing the door-to-door screening will be aired daily on the local radio station (Korogocho FM) over a 2-week period from the start of the intervention.

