The SCALE UP study investigators will train the CHWs to assess the study participants’ level of engagement in risky lifestyle behavior including tobacco use, alcohol misuse, physical activity levels and dietary habits. CHWs will also be trained in performing basic anthropometric and clinical measurements including height, weight, waist and hip circumference, blood pressure and blood glucose. They will be provided with the appropriate equipment for the clinical measurements (see Table 1). Also, each CHW will be trained to provide brief counselling assistance (BCA) of healthy lifestyle modification using the six As approach –*Ask*, *Advice*, *Assist*, *Arrange*, *Agree and Affirm*[31]. Traditional BCA does not include the sixth A (Affirm) as a separate entity. However, the SCALE UP team has included this component to emphasize the need for CHWs to encourage study participants to continue with any healthy lifestyle behavior in which they reported being currently engaged. All eligible and consenting study participants will receive BCA during the door-to-door visit. If the eligible adult(s) are not at home, the CHWs will try to visit another time, with a maximum of two attempts.

**Table 1 T1:** List of screening equipment

**Equipment**	**Units**
SECA 201 circumference measurement tape	*cm*
SECA 874 flat scale electronic	*kg*
SECA 214 stadiometer transportable	*cm*
OMRON M6 blood pressure machine	*mmHg*
ACCUCHECK glucometer and test strips	*mmol*/*l*

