### Sample size considerations

In order to detect a 5% reduction at endline in the proportion of adults aged 35 years and above who are at moderate or high risk of CVD [38,39] in the intervention population versus no change in the control population (assuming both populations have similar start prevalence at 25%), we need 2,927 respondents in both intervention and control sites, using an alpha of 0.05 and power (1-beta) of 0.90. Taking into account a non-response rate of 10%, we will approach 3,220 individuals per cross-sectional study—that is, 1,610 per site at baseline and endline surveys, respectively.

The sampling frame will be based on the most recently updated NUHDSS database. This database contains details of about 72,000 individuals including names, locations, gender, dates of birth and residential status in both slums. In the control site, we will use computer randomization (STATA® statistical software) to select the 1,610 individuals aged 35 years and older per site for each cross-sectional survey.

In the intervention site, the same computer randomization process will be followed. However, unlike the control site, the 1,610 individuals to be included in the cross-sectional survey analysis will be collected retrospectively. In other words, the intervention package will be delivered to all adults aged 35 years or older in the intervention site—that is, 6,780 individuals according to the DSS database (as at 15 June 2012).

At the clinic level, we calculated that in order to detect a 10 mmHg reduction in blood pressure (at 20 mmHg standard deviation, alpha of 0.05 and 1-β on 0.9), about 44 participants are needed. However, it is projected that approximately 1,350 participants (out of 6780) will be referred from the door-to-door visit. This number is derived from a 20% prevalence of hypertension among adults aged 35 years and older in the study area [27]. We estimate that roughly half of these 1,350 participants, being 675, will continue visiting the clinic for treatment. Hence, this number of people is more than sufficient for the analysis of our main primary outcome at the clinic level.

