Intervention cost will be estimated using a micro-costing approach where feasible. Micro-costing is a process of systematically identifying and measuring resource utilization using a process tracking system and interviews with the local program team [42]. According to the Panel on Cost-Effectiveness in Health and Medicine, the theory and process of valuing costs through a micro-costing methodology rest on a three-step approach: identification, measurement and valuation of resources used [43]. For other non-specific costs, gross costing methods will be considered. Once resource utilization has been measured, the component-specific costs of the intervention can be computed by multiplying the quantity of each type of resource consumed by unit costs. The component-specific costs can be summed up to get the total costs of the intervention [42]. Finally, the outcome of this analysis will be the average cost for CVD risk reduction per participant per year. Data on costs and timings will be collected from the preparation of the intervention until the end of the intervention period. A yearly discount rate of 3% will be used for long-term modeling and projections [44]. Estimations will be extended to project the cost-effectiveness of the intervention package were it implemented on a national scale.

Finally, in order to determine the scalability and feasibility of the intervention package, a comprehensive process evaluation will be conducted involving analysis of operational data as well as qualitative sub-studies with beneficiaries and other relevant stakeholders such as local policy makers.

Additionally, since the package is to be implemented in a private health sector setting, it will be important to examine essential aspects of the intervention package that are needed to translate the package to the public sector.

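### The two waves are planned as unlinked cross-sections, although individuals can be identified and most Korogocho endline respondents should have an own baseline reading; linking them would gain moderate precision at almost no cost

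*Protocol article*

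**What the plan says.** Data management states that "there will be two cross-sectional surveys (before and after, 12 months apart". Sample size considerations uses computer randomization "to select the 1,610 individuals aged 35 years and older per site for each cross-sectional survey", and derives the number from an unpaired comparison of two proportions. The Impact formula under Analysis uses only the outcome value in each site and wave. No link between a person's two readings is planned or ruled out, and no standard-error method is given.

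The same article shows that linkage is possible. On the sampling frame it says: "This database contains details of about 72,000 individuals including names, locations, gender, dates of birth and residential status in both slums". In Korogocho, "the 1,610 individuals to be included in the cross-sectional survey analysis will be collected retrospectively", because "the intervention package will be delivered to all adults aged 35 years or older in the intervention site", put at 6,780 people. The household visits are "to conduct screening of each eligible adult aged 35 years and above in the intervention slum", and blood pressure is among the measurements. Coverage has a limit: if adults are out, "the CHWs will try to visit another time, with a maximum of two attempts".

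**The concern.** Two samples of 1,610 from one finite list of several thousand people share members. Readings on the same person a year apart are positively correlated, so a variance formula for independent waves is too large for the overlap that the design creates. In Korogocho the loss goes further: baseline readings should exist for most adults, but only 1,610 records are pulled for the baseline cell, and an endline respondent's own earlier reading is not used. The stake is efficiency, not validity. It matters because the planned size gives the double difference far less than the stated 90% power (step 2 of the working), and the identifier and the retention of all screening records have to be settled when data are collected.

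**Working it through.** **Inputs from the article.** 25% at baseline in both sites, 20% at endline in the intervention site, alpha 0.05, power 0.90, 2,927 respondents, 10% non-response, 1,610 per site and wave, 6,780 Korogocho adults (Sample size considerations). About 72,000 residents, split almost equally (Setting); 21% above 35 years (Inclusion criteria).

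**Assumptions.** Within-person correlation rho = 0.3, 0.5, 0.7. Korogocho baseline records about 6,100 (6,780 × 0.9 = 6,102). 80% of Korogocho endline respondents linked. The Viwandani frame is not given: 0.21 × 36,000 = 7,560, or 0.21 × 72,000 − 6,780 = 8,340.

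**1. The stated size.** Per site, [1.96·√(2 × 0.225 × 0.775) + 1.2816·√(0.1875 + 0.16)]² / 0.05² gives 1,464; the unrounded total is 2,927.4. Then 2,927 × 1.10 = 3,220. Both figures reproduce, as one unpaired comparison of 25% with 20%.

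**2. Double difference, independent waves.** With n = 1,610 × 0.9 = 1,449 per cell, SE = √[(3 × 0.1875 + 0.16)/1,449] = 2.23 percentage points. Power for 5 points is Φ(0.05/0.0223 − 1.96) = 61%.

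**3. Chance overlap.** Korogocho: 1,610/6,780 = 24%. Viwandani: 1,610/7,560 = 21% (19% with 8,340). After 10% non-response at baseline these become f_K = 21% and f_V = 19% (17%). The true variance relative to the independent formula is 1 − rho(f_K + f_V)/2 = 0.94, 0.90, 0.86. The SE is overstated by 1/√ratio − 1 = 3%, 5%, 8%.

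**4. All Korogocho baseline records, unlinked.** Treating the cells as equally variable, here and below, and using no Viwandani overlap: ratio = (3 + 1,449/6,100)/4 = 0.81; power 70%.

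**5. Same estimate, variance clustered on person.** Ratio = [3 + (1,449/6,100)(1 − 2 × 0.8·rho)]/4 = 0.78, 0.76, 0.74; power 72%, 73%, 74%. The point estimate is that of step 4.

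**6. Own-baseline values used as well.** Ratio = [(1 − 0.8·rho²) + (1 − 0.8·rho)² × 1,449/6,100 + 2]/4 = 0.77, 0.72, 0.66; power 73%, 75%, 78%. This formula takes linked and unlinked people to have the same baseline mean.

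**7. What no person-level SE contains.** For systolic pressure with SD 20 mmHg (stated only for the clinic calculation), the unlinked SE is 2 × 20/√1,449 = 1.05 mmHg. With rho 0.5 and linkage of 90% in Korogocho and 20% in Viwandani it is 1.05 × √[(0.55 + 0.90)/2] = 0.89. An assumed drift SD of 1 mmHg per slum adds 2 × 1² to the variance: √(1.05² + 2) = 1.76 and √(0.89² + 2) = 1.67.

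**The case against.** Repeated cross-sections are a valid design for an effect on the current population, and the variance estimator may be left to an analysis plan. Both points stand. It is also not certain that the waves are meant to be unlinked: Table 2 marks socio-demographic data at baseline only, and the abstract can be read as one sample seen twice. What remains is the unpaired planning and sizing, with no provision for an identifier or for use of the full Korogocho screening data.

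Three stronger readings are tempting and should not be made.

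- A reader might infer that nearly every Korogocho endline respondent has a baseline reading. The article gives no coverage or turnover figure, and two visit attempts, refusal, in-migration and people reaching 35 all reduce it. Most is as far as it goes.
- A reader might infer that the reported error bars will be too wide. No SE method is stated, so this is conditional on an independent-waves analysis. With one slum per arm, total uncertainty may instead be understated (step 7).
- A reader might infer that the costing needs within-person change, because "the outcome of this analysis will be the average cost for CVD risk reduction per participant per year". An average follows from group means, and Analysis bases effectiveness on population-level changes. The costing gives no support to this point.

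The other side is also right about the source of the gain. Of the variance reduction in step 6, 0.19 comes from using all Korogocho baseline records; linkage by own-baseline values adds about 2-8 power points over step 4, depending on rho. Korogocho baselines missing through non-contact, refusal, in-migration or ageing-in are not missing at random, and linkage is far more complete in Korogocho than in Viwandani, so linked records over-represent stayers unevenly between the arms.

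**Conclusion.** The point holds as a loss of efficiency; the planned contrast is not invalid. An independent-waves analysis would overstate the person-level SE by about 3-8% from chance overlap and leave Korogocho baseline data unused. Full use of those records takes power for the 5-point effect from about 61% to 70%; person clustering gives about 72-74%, and own-baseline values about 73-78%. The overlap rests on the stated sample sizes and an approximate Viwandani frame. The gains rest on assumed rho, 6,100 baseline records and 80% linkage, none of which the article gives. The target of 90% is not reached by any of these routes, because the size was computed for a two-group comparison and not for the double difference. That is the larger problem, and linkage only narrows it.

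**What to change.** 1. Carry the surveillance person identifier on every survey and screening record in both slums, and report the share linked per site.
2. Use all Korogocho baseline screening records as the baseline cell, not only 1,610 of them.
3. Estimate the site-by-wave effect on all respondents, linked or not, so that the target stays current residents. Use errors clustered on person for the risk proportion and a person-level mixed model for systolic pressure, and adjust for age where possible, since linked people are a year older at endline. A mixed model also draws on own-baseline readings, so show the person-clustered estimate for systolic pressure too.
4. Report the unlinked Impact beside these results, and label any own-baseline-adjusted estimate as supportive, for the reasons of uneven linkage and non-random missing baselines.
5. State that none of these standard errors includes slum-level drift.

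The cost is record linkage on a list that the study already uses for sampling, plus analysis wording. No new participants or visits are needed.

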** *Clinic based* **			
Physical measurements (weight, height, waist and hip circumference, blood pressure)	X	X	X
Lifestyle modification advice		X	
Drug prescriptions and side effects		X	
Morisky adherence score		X	
** *Operational data* **			
Costs		X	
Timesheets		X	

All data will be entered onto electronic data collection forms pre-loaded into Mecer® Netbooks and stored in an SQL database managed by the data unit of APHRC. To ensure data quality, the field staff will be trained in interviewing techniques and how to use the Netbooks. Data collection forms will be translated into Swahili and back to English for consistency. Interviews will be conducted in Swahili—the main lingua franca in the study areas. Supervisors will be recruited to conduct spot checks of at least 5% of randomly selected interviews conducted by each field staff they supervise. They will also perform a random check of 5% of data collection forms completed by field staff. Forms will be checked for errors, missing information and inconsistent responses, and, where necessary, field staff will be required to revisit a study participant in order to clarify any erroneous information.

At the intervention clinic, qualified data entry clerks will be trained to double-capture all clinic data collected by the nurses and clinical officers during the patient consult. Clinic data will also be electronically captured using Netbooks.

Finally, cost data will be collected on an on-going basis in order to feed into the cost-effectiveness analysis of the intervention package. This will be done through an adapted checklist to collect information on costs and related time spent in all aspects of implementing the intervention package.

#### Primary outcomes

The primary outcomes of the SCALE UP study are:

1. The difference in change in the proportion of the study populations (intervention and control slums) that are at high risk of CVD (defined as >10% risk of developing cardiovascular event in the next 5 years based on the method for assessment of cardiovascular disease risk by Gaziano et al. [33]).

2. The difference in change in mean systolic blood pressure in the study populations (intervention and control slums).

3. The change in mean systolic blood pressure among participants attending the local clinic (intervention slum only).

4. The net cost of the intervention package per disability-adjusted life year gained (intervention slum only).

#### Secondary outcomes

1. Prevalence of hypertension in the intervention and control slums.

2. Proportion of hypertensive respondents who are on treatment, and under control, in the intervention and control slums.

3. Proportion of high-risk participants who sought first time treatment after screening and referral.

4. Prevalence of behavioral and biological CVD risk factors: smoking, physical exercise, diet, alcohol intake, body mass index, waist circumference and waist-to-hip ratio in the intervention and control slums.

### Sample size considerations

In order to detect a 5% reduction at endline in the proportion of adults aged 35 years and above who are at moderate or high risk of CVD [38,39] in the intervention population versus no change in the control population (assuming both populations have similar start prevalence at 25%), we need 2,927 respondents in both intervention and control sites, using an alpha of 0.05 and power (1-beta) of 0.90. Taking into account a non-response rate of 10%, we will approach 3,220 individuals per cross-sectional study—that is, 1,610 per site at baseline and endline surveys, respectively.

The sampling frame will be based on the most recently updated NUHDSS database. This database contains details of about 72,000 individuals including names, locations, gender, dates of birth and residential status in both slums. In the control site, we will use computer randomization (STATA® statistical software) to select the 1,610 individuals aged 35 years and older per site for each cross-sectional survey.

In the intervention site, the same computer randomization process will be followed. However, unlike the control site, the 1,610 individuals to be included in the cross-sectional survey analysis will be collected retrospectively. In other words, the intervention package will be delivered to all adults aged 35 years or older in the intervention site—that is, 6,780 individuals according to the DSS database (as at 15 June 2012).

At the clinic level, we calculated that in order to detect a 10 mmHg reduction in blood pressure (at 20 mmHg standard deviation, alpha of 0.05 and 1-β on 0.9), about 44 participants are needed. However, it is projected that approximately 1,350 participants (out of 6780) will be referred from the door-to-door visit. This number is derived from a 20% prevalence of hypertension among adults aged 35 years and older in the study area [27]. We estimate that roughly half of these 1,350 participants, being 675, will continue visiting the clinic for treatment. Hence, this number of people is more than sufficient for the analysis of our main primary outcome at the clinic level.

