### Intervention community

Korogocho slum, which has eight villages, each with between 3,000–5,000 residents, will be the intervention site. This slum has one centrally located private health facility with a reliable track record of providing primary health services. This facility is known as *Provide International Clinic*. It is well known in the slum and, although most patients still make out-of-pocket payments for services received, the clinic offers non-profit services at highly subsidized (through donor funding) costs to residents. There are no physicians or medical officers present at this clinic. Nurses and clinical officers (health personnel with a diploma in clinical medicine) provide consultations. However, the facility does not typically provide primary preventive services for CVD such as screening and treatment of hypertension. The location of this clinic and the absence of primary preventive services for CVD guided our choice of intervention site.

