### Control community

Viwandani slum will be the control site. There are seven villages in Viwandani with approximately 2,000–4,000 residents each. Unlike Korogocho, Viwandani does not have a centrally located health facility. The main health facility serving Viwandani is located on the outskirts of the slum. This facility is publicly owned and represents the usual standard of care for CVD that is available to underserved slum communities in Nairobi, thus making Viwandani the appropriate ‘control’ site in comparison with Korogocho. The clinic in Viwandani operates a weekly CVD clinic where approximately 30 patients with uncomplicated hypertension and/or diabetes from Viwandani slums are seen on each clinic day. Like the facility in Korogocho, the Viwandani clinic is also run by nurses and clinical officers.

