### Analysis

Due to the fact that the slums are part of a large demographic surveillance site and therefore not randomized, we will use the double-difference method [40] to evaluate the primary outcomes in the intervention versus control sites. In this approach, Impact = (Y_p(t>0)_ – Y_p(t=0)_) – (Yc_(t>0)_ – Yc_(t=0)_) where Y_p_ is the primary outcome in the intervention group and Y_c_ is the outcome in the control group. For the double-difference method to work, it is essential that there are at least two pre-intervention data points. In addition, having many preintervention data points allows for the detection of shifts or interruptions in trends (if any) after the introduction of an intervention. A cross-sectional study conducted in the NUHDSS from 2008–2009 provides one time point of pre-intervention data on CVD risk in the intervention and control slums [27]. Note that cardiovascular risk reduction will be calculated by entering the outcomes in a non-laboratory-based CVD risk assessment chart [33]. Regression analyses will also be performed to investigate the association of each risk factor with the main outcomes such as blood pressure. Specifically, multivariate analyses will be used to adjust for known or perceived confounding variables while comparing outcomes between intervention and control sites. Prior to this, descriptive statistics will be applied to compare characteristics of the intervention and control sites. For behavioral risk factor analysis, we will use an interpretive descriptive approach with matrix comparisons between groups (such as sex, age group and site).

Cost-effectiveness analysis will be conducted according to the WHO framework for cost-effectiveness analysis [41]. This framework will consider intervention effectiveness data based on changes in blood pressure and overall predicted cardiovascular risk at the population level, as well as cost data on the intervention. The overall cost-effectiveness of the intervention package will be calculated in terms of DALYs averted per US dollar.

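### The 0.90 power is that of an endline two-proportion comparison of independent respondents; the double difference has about 61%, and less with village-by-wave correlation

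*Protocol article*

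**What the plan says.** The section Sample size considerations takes the combined category of moderate and high risk as its outcome and sets this aim: "In order to detect a 5% reduction at endline in the proportion of adults aged 35 years and above". The effect is defined as a fall "in the intervention population versus no change in the control population". The starting level is fixed by "assuming both populations have similar start prevalence at 25" per cent. It concludes: "we need 2,927 respondents in both intervention and control sites, using an alpha of 0.05 and power (1-beta) of 0.90". The only inflation is 10% for non-response, giving 3,220 per survey and 1,610 per site. Individuals are drawn by computer from the surveillance database across the whole site.

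The analysis is a different contrast. Under Analysis, "we will use the double-difference method [40] to evaluate the primary outcomes in the intervention versus control sites". That section gives the formula for the point estimate and mentions multivariate adjustment. It names no standard error or test.

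On structure, under Intervention community: "Korogocho slum, which has eight villages, each with between 3,000–5,000 residents, will be the intervention site". Under Control community: "There are seven villages in Viwandani with approximately 2,000–4,000 residents each". CHWs are recruited for each Korogocho village: "These CHWs will then be trained and equipped to perform the door-to-door visits and screening exercise in their respective villages in the intervention slum". They also coordinate village support groups (Promoting long-term adherence) and take the survey's physical and clinical measurements in Korogocho. Field assistants take them in Viwandani (Data management).

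**The concern.** Two features of the design are absent from the power statement.

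- **The contrast.** A double difference carries sampling error from four site-by-survey estimates, not two. A sample sized for the endline difference alone is too small for it.
- **The correlation.** In Korogocho, delivery and measurement both run through village CHWs. A strong or weak team, or a habit in taking blood pressure, moves a whole village at one survey. That part of the variation is averaged over 8 or 7 villages, not over some 1,460 people.

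At stake are a planned power well below the stated one for the risk outcome and, if the tests follow the sample size in treating people as independent, intervals that are too short for primary outcomes 1 and 2.

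**Working it through.** **Inputs from the article:** 25% at start, 20% at endline in the intervention site, no change in control; alpha 0.05; power 0.90; 8 and 7 villages. **Assumed, because the article gives neither:** village ICC (ρ) and between-wave correlation of village effects (c). The two surveys are treated as separate samples.

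**1. The plan's own figure.** The mean proportion is 0.225.

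n per site = [1.960 × √(2 × 0.225 × 0.775) + 1.2816 × √(0.25 × 0.75 + 0.20 × 0.80)]² / 0.05² = [1.960 × 0.5906 + 1.2816 × 0.5895]² / 0.0025 = 1,463.7

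The total is 2 × 1,463.7 = 2,927.4, which is the printed 2,927 with no design effect. Then 2,927 × 1.10 = 3,219.7, the printed 3,220. The article does not state sidedness; the two-sided version reproduces the figure and the one-sided version (2,386) does not.

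**2. Double difference, full independence.**

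- Variance = (3 × 0.25 × 0.75 + 0.20 × 0.80) / 1,464 = 0.7225 / 1,464 = 0.000494, so SE = 0.0222.
- Power = Φ(0.05 / 0.0222 − 1.960) = Φ(0.291) = 61%.
- For 90%: (1.960 + 1.2816)² × 0.7225 / 0.05² = 3,037 per site per survey, about twice the plan.

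**3. Adding village-by-wave variation.** The part of a village's level that is the same at both surveys cancels. The part that changes has variance τ² = ρ(1 − c) × 0.1875 and adds 2τ²/8 + 2τ²/7 = 0.536τ² to the variance of the double difference. With no effect, the independent variance is 4 × 0.1875 / 1,464 = 0.000512 (SE 0.0226). Within-village sampling contributes (1 − ρ) times the independent variance.

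- ρ = 0.01, c = 0.9: τ² = 0.0001875; true variance = 0.99 × 0.000512 + 0.000100 = 0.000608; SE 0.0246, or 1.09 times the independent one. False-positive rate = 2[1 − Φ(1.960 / 1.09)] = about 7%.
- ρ = 0.01, c = 0.8: τ² = 0.000375; true variance = 0.000507 + 0.000201 = 0.000708; SE 0.0266, or 1.18 times. False-positive rate about 10%.

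Simulation (20,000 trials per setting) agrees. The last column is the power of a t test on village changes with 8 + 7 − 2 = 13 df.

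| ρ | c | False-positive rate, independent test | Power, village-level test |
|---|---|---|---|
| 0 | – | 5% | about 55% |
| 0.01 | 0.9 | about 7% | 48% |
| 0.01 | 0.8 | about 10% | 42-43% |
| 0.05 | 0.9 | about 16% | 31% |
| 0.05 | 0.8 | about 25% | 22-23% |

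**4. Where the power goes (ρ = 0.01, c = 0.9).** From 90% to 61% is the change of contrast, 61% to 55% is the use of 13 df, and 55% to 48% is village-by-wave correlation.

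**5. One slum per arm.** The village-level test holds 5% in these simulations only because they contain no slum-wide change. If each slum's level varied between surveys with an assumed SD of one percentage point, the variance would gain 4 × 0.01² = 0.0004. The independent test would then reject in 2[1 − Φ(1.960 × √(0.000512 / 0.000912))] = about 14% of null trials. Village-level inference does not detect this variation either.

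**The case against.** A reader might infer that the article itself analyses respondents as independent, so that its error bars are too narrow. It does not say so. The Analysis section gives a point estimate and no variance method, which may stand in an analysis plan that is not shown. The false-positive rates above are therefore conditional: they apply if the test follows the assumption built into the sample size.

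A reader might also blame clustering for the whole loss from 90%. Step 4 shows otherwise, since most of it comes from sizing the endline contrast. For the same reason it would be wrong to say that 0.90 simply assumes independent respondents. Under independence the double difference has 61%.

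The strongest counter-argument concerns the target of inference. Individuals are sampled across each whole slum, every village is in the frame, and the outcomes refer to the two slum populations. For describing those two populations, villages act as strata and individual sampling creates no village design effect. Several components (radio, the single clinic, text messages) are slum-wide, digital devices and three readings limit measurement differences, and no village assignment is stated for Viwandani's field assistants. All of this stands and argues for a modest correlation. It does not remove the point. Attributing a change to the package, and projecting it to a national scale as the article intends, requires judging it against variation between CHW teams and villages over time.

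Finally, village-level inference does not solve the assignment of one slum per arm. That is correct, and the plan should say so.

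**Conclusion.** The concern holds in this form. The printed power of 0.90 belongs to an endline comparison of independent people, not to the double difference that the plan will estimate. For the risk proportion, the double difference has about 61% under full independence; this follows from the article's own inputs and needs no assumed correlation. A later analysis plan can supply a variance method but cannot make the printed 0.90 correct.

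The further loss from village-by-wave correlation, and the excess of false positives if respondents are treated as independent, have a clear direction but an uncertain size. At an assumed ICC of 0.01 and between-wave correlation of 0.8-0.9 they are 42-48% power for a village-level test and a 7-10% false-positive rate; a larger ICC makes both worse. The power figures concern outcome 1 only, because the article gives no population-level sample size for systolic pressure. The point about standard errors applies to outcomes 1 and 2.

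**What to change.** - **Sample size considerations:** say that 2,927 and 0.90 refer to the endline two-proportion comparison. Restate the power as that of the double difference (about 61% with 1,464 per site per survey under independence), and tabulate it over a stated range of village ICC and between-wave correlation.
- **Analysis:** state that outcomes 1 and 2 are estimated by a site-by-wave regression with village-clustered standard errors and a few-cluster correction (t on 13 df or wild cluster bootstrap). Use individual-level or size-weighted estimation, so that the estimand stays the slum population; an unweighted mean of village changes would alter it, because the villages differ in size.
- **Limitation:** add that with one slum per arm this interval is a lower bound on uncertainty and cannot separate a slum-specific change from the effect of the package.

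The cost is wording, wider intervals and a lower stated power. No new respondents or data should be needed, because the surveillance database holds locations from which village of residence should be obtainable.
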